**Fig. 5 Fig5:**
[figure not shown]
ATM conceptual framework

Of the seven *talukas* which qualified for the intervention, we randomly chose three *talukas* using the online random number generating tool (Available at http://www.random.org/; see Additional file 2). The three *talukas* chosen were Koratagere, Sira and Turuvekere. Some characteristics of the three *talukas* are presented in Table 2. PHCs across the three *talukas* were randomly assigned to one of three arms (A, B and C) of the study intervention. In Arm A, PHCs will receive a package of interventions to optimise service delivery, while Arm B, they will receive Arm A package as well as an additional package of interventions to strengthen existing community participation platforms for organising NCD care at PHC. PHCs in Arm C will be the control. The package of activities in A, B and C are described in Table 3. A detailed description of the intervention and the underlying assumptions behind the activities proposed is provided in Additional file 3 and step-wise plan of rolling out of the intervention is presented in Fig. 6.

**Table 2 Tab2:** Characteristics of study talukas

Characteristics	Koratagere	Sira	Turuvekere
Area	652 Sq km	1552 Sq km	778 Sq km
Population	160,952	301,473	174,297
Number of private pharmacies	19	30	22
General adult literacy rate	71 %	67 %	73 %
Number of PHCs	11	17	11
Average population per PHC	14,500	18,000	16,000
Number of private hospitals/clinics	21	64	18
Number of PHCs with qualified MBBS doctors (of) total number of PHCs in *taluka* (as on March 2014)	11 of 11	15 of 17	10 of 11

(Source: Census 2011)

**Table 3 Tab3:** Description of activities planned under the study intervention arms

Intervention arm	Intervention name	Intervention input	Activities
A	Optimise service delivery	Orientation training & workshop for PHC medical officers	Training on standard treatment guidelines for NCDs, rational prescription, maintaining treatment cards for patients with NCDs and conduction of health days for NCD care.
		Training workshop for pharmacists	Training on need assessment for medicines, counselling patients on medicines and their side effects and non- drug treatment, indenting for medicines and record keeping at PHCs.

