##### Facility survey tool

For the facility level survey, we used a modified version of Level II survey tool included in the WHO Operational Packages for Monitoring and Assessing Country Pharmaceutical Situations (World Health Organization [39]; see Additional file 5). This tool shall be used to collect data from PHCs, private pharmacies and the district medicines warehouse. For the facility survey tool, we used the Karnataka state standard treatment guidelines to finalise a list of medicines that are supposed to be used for NCDs at PHC level. 11 medicines were included in the survey tool.

The facility survey will assess various aspects of NCD drugs such as the availability of key essential medicines for diabetes and hypertension, their stock-out duration, record-keeping at the facility, conservation conditions and handling of medicines, patient care and prescribing practices, price, storing, availability of standard treatment guidelines and essential medicines list.

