##### Exit interview tool

The exit interview tool will collect data about average number of dispensed medicines per prescriptions and the travel cost borne by NCD patients (see Additional file 6). The tool will assess how many of the prescribed medicines were dispensed at the PHC and if the medicines were adequately labelled (the label should contain the medicine’s name and dosage), if the patients knew about the dosage and duration of all dispensed medicines, and how much the patient paid out-of-pocket for medicines and/or in non-diagnostic fees.

This tool was translated to the local language Kannada and was verified by a native speaker of Kannada. The tool was further modified based on two phases of piloting of the tool.

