#### Outcome estimation

Outcomes (see Table 9) will be reported as effects of said interventions and represented as risk ratios and odds ratios with 95 % confidence interval.

**Table 9 Tab9:** Measures (indicators) for primary and secondary outcome of interest

Factors to be measured	Indicator
Primary outcome of interest	
Improved and continuous availability of generic drugs at PHC	Percentage of PHC where all generic medicines for NCD patients adequately available in last three months
Increased and regular access to quality medicines for patients with NCD	Percentage of NCD patients/patient groups visit intervention PHC in last three months
Out-of-pocket expenses among patients with NCD	Percentage reduction in median OOP expenditure on medicines per year among NCD patients.
The marginal cost of the intervention to that of the outcome	Incremental cost effective ratio
Improved compliance to standard treatment guidelines by the PHC	Percentage MOs followed prescription practices as per the standard treatment guidelines.
Improved demand of generic drugs among the patients	Percentage increase in patients availing generic drugs from the PHC compared to what it was at three months back
Improved utilization of medicines among NCD patients	Percentage of NCD patients/ patient groups obtained complete and regular medication for last three months.
Secondary outcome of interest	
Better coordination among health staffs with regards to NCD patient group formation	- Percentage increase in number of patient groups formed. - Percentage increase in number of new diabetes patients registered in last three months for a given PHC. - Percentage increase in number of new hypertension patients registered in last three months for a given PHC.
Better drug procurement	Percentage PHCs where drug procurement is up to date for the last quarter.
Conduction of NCD clinics	Percentage PHCs conduct NCD days in last three months
Better reporting and recording by the pharmacists at PHC	Percentage PHCs where medicines were dispensed as prescribed

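### Table 9 measures pharmacist reporting and recording by a dispensing indicator, so a change in it cannot be reported as an effect on recording

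*Protocol article*

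**What the plan says.** In the protocol article, section Outcome estimation, each row of Table 9 pairs a factor with one or more indicators. The last secondary row names the factor "Better reporting and recording by the pharmacists at PHC" and gives it a single indicator, "Percentage PHCs where medicines were dispensed as prescribed". The sentence introducing the table fixes its use: "Outcomes (see Table 9) will be reported as effects of said interventions".

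Three other places bear on this row:

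- Table 3 (intervention activities) includes a pharmacist workshop in the Arm A package, which Arm B also receives. Among its topics are "indenting for medicines and record keeping at PHCs".
- The section Facility survey tool lists what the survey assesses at each facility. The list includes "their stock-out duration, record-keeping at the facility", as items separate from the availability of key medicines.
- The section Exit interview tool describes patient interviews at the PHC: "The tool will assess how many of the prescribed medicines were dispensed at the PHC".

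**The concern.** The label and the indicator in this row describe different things. The label concerns what the pharmacist writes down and reports. The indicator concerns whether the medicines given match the prescription.

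The row will be read as an effect estimate. The intervention also works on drug supply: Table 3 includes advocacy to secure supply through the routine chain, the district plan or local funds. If supply improves and dispensing follows, this row would show pharmacists recording better although no register need have changed. In the other direction, real gains from the record-keeping training could be hidden by stock-outs. The interpretation of a trained behaviour would rest on a quantity that does not measure it.

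**Working it through.** No formula applies, and the plan gives no figure to reproduce. The check compares what the row claims to measure with what its indicator can register.

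**Step 1. Is recording a real target?** Yes. Record keeping is a named topic of the pharmacist workshop in Table 3, so an outcome on it is reasonable and its indicator matters.

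**Step 2. Does the indicator contain a recording element?** Not in its wording. Nothing elsewhere in the article defines dispensing against prescription as a measure of record completeness or accuracy.

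**Step 3. Can label and indicator diverge?** Consider four kinds of PHC:

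| Records | Medicines given match prescription | Reading from Table 9 | Reading correct for recording? |
|---|---|---|---|
| Good | Yes | Good | Yes |
| Good | No (for example, a stock-out) | Poor | No |
| Poor | Yes | Good | No |
| Poor | No | Poor | Yes |

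The second and third rows are both ordinary situations. The indicator can therefore mislead in either direction, and a difference between arms or over time cannot be assigned to recording.

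**Step 4. Does another Table 9 row cover recording?** No. The nearest is the procurement row, which asks whether drug procurement is up to date. That is a different activity and has its own label. The clinic and procurement rows pair label and indicator sensibly, so the mismatch does not look like a general feature of how the table was built.

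**Step 5. Does the study hold data on recording?** Yes. The facility survey assesses "record-keeping at the facility" as an item distinct from availability and stock-out duration. The section Facility survey reports that all 39 PHCs were surveyed, and Study design and conceptual framework states that PHCs are surveyed at baseline and endline. Dispensing against prescription is described under a different tool, the exit interview. The study thus treats the two concepts separately at data collection and merges them only in Table 9.

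**The case against.** The strongest reply is that this is one loosely labelled secondary row and that little information is lost. Most of the supporting points stand.

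- **Recording data are not lost.** A reader might infer that a failure of recording would go unseen. The document does not support that. The section Bivariate analysis says facility characteristics at baseline and endline will be compared across arms and talukas, and record-keeping is one of the facility items collected. What is wrong is the declared outcome, not the absence of data.
- **The data source is not stated.** A reader might infer that the indicator is wholly insensitive to records. Table 9 does not say where the indicator comes from or when a PHC counts as passing, and the tools are in additional files not shown here. If it were drawn from PHC dispensing records, a PHC without records might not be able to pass. Even then the indicator would require records to exist and would not measure their quality.
- **It does not duplicate the availability outcome.** The primary availability row asks whether all generic NCD medicines were adequately available over three months. A PHC lacking one drug can still dispense everything prescribed, and a fully stocked PHC can dispense wrongly. The two depend on stock in part but are distinct.
- **The training may affect dispensing too.** The same workshop covers need assessment, indenting and counselling, which could plausibly change what is dispensed. That makes the indicator a fair dispensing outcome. It does not make it a recording outcome.
- **No size can be attached.** It is tempting to compute how far the indicator would move for a given change in stock. The indicator is a percentage of PHCs with no stated pass threshold, and the document gives no stock levels or number of medicines per prescription, so any figure would rest on invented inputs.

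None of these points supplies a link from the indicator to the label.

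**Conclusion.** The concern holds in a limited form. The indicator fixed for this row depends on stock, prescribing and dispensing and does not measure the completeness or accuracy of records. A change in it cannot be reported as an intervention effect on recording.

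The consequence is confined to the interpretation of one of the four secondary rows. None of the seven primary rows, the sample size or the difference-in-difference estimation is touched. The conclusion needs no assumption about effect size or stock levels. It rests on the wording of the Table 9 row and on the absence of any definition in the article that ties dispensing to record quality; it holds whether the indicator comes from patients or from PHC records. Because the pairing is stated in the table, it is not a detail left to a later analysis plan.

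**What to change.** 1. Base the reporting and recording row on the record-keeping item of the facility survey at all 39 PHCs, in whatever form it was recorded at baseline, and compare baseline with endline across arms.
2. Give the dispensing indicator its own secondary row with a dispensing label, and state its data source and the rule by which a PHC passes.
3. If the baseline record-keeping item proves unusable, relabel the present row as a dispensing outcome and draw no conclusion on recording from it.

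The cost is an edit to Table 9 and a short scoring definition, with no new type of data. The new indicator should not rely on a check that may not have been made at baseline. The section Facility survey says only that stock-out duration and indenting price were physically verified, and baseline collection is already complete. A comparison of stock registers with a physical count, for example, cannot be assumed to have a baseline value. Step 3 is the only option that is certain to need wording alone.

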#### Qualitative data analysis

All the process documentation data and the baseline and endline interview transcripts will be managed through uploading in a secure and password-protected account in Evernote, a cloud-based data storage software that allows for tagging and organising various forms of data automatically, for place, type of data and coordinates [45]. This data will be directly imported into NVivo for coding.

The qualitative data analysis will draw from the principles of theory-driven approach, in this case starting with the initial programme theory. We will analyse the qualitative data by examining the extent to which the intervention designers’ assumptions were borne out, especially looking for alignments as well as contradictions to these programme theory assumptions. In doing so, we will borrow from wider literature on how and why interventions such as this one have been studied in literature, as well as scanning our data for micro and meso level contextual factors that affected programme performance and/or outcomes [26]. We will thus refine the initial programme theory enriching it with the contextual understanding of the intervention in order to explain how the intervention worked (where it did) and under what conditions it worked. The resulting refined programme theory at the end of the intervention will be useful in understanding how local health systems such as Tumkur respond to resources that such interventions provide.

## Discussion

### Understanding the *why* and *how* of interventions

Healthcare organisations and systems are complex entities, which do not respond uniformly and predictably to a given policy. Feedback loops and path dependence often result in policy failures or inadequate response, while there could also be unintended and unforeseen consequences of interventions. We have developed an intervention based on the gaps in the present health system that need to be addressed for the above policies to result in improved access to medicines for people with NCDs.

Our intervention is being implemented at the district level in partnership with the district health services. It could be described as a complex intervention in view of the involvement of actors at various levels of the health system with varying interests, powers and relationships. Innovative health services interventions need to be designed in LMICs to better understand the conditions that could enable improvement in complex health systems. Hence, integrating experimental study designs (effectiveness) with qualitative methods (process) is crucial. Our study provides a model for strengthening health services for NCDs and identifying the necessary conditions for improvements. By taking into consideration several components of the health system (governance, service delivery, resource planning and community) and trying to understand them, our study aims to generate evidence for health planners on how to optimise health services to improve access to medicines in a particular kind of setting.

### Medicines: from availability to access

In India, as in many other LMICs, various issues hinder access to medicines. The access issue is more acute for NCD patients due to their need for lifelong supply. Issues related to procurement, management of supply chain and the governance of drugs procurement systems in the state level are crucial to ensuring availability of medicines at PHCs. Since drugs procurement and supply is often relatively centralised in many states, those states that have implemented reforms of their procurement systems are better-off with respect to ensuring availability of medicines in PHCs [46]. However, in addition to reforms at the state level, district and sub-district level capacity and performance issues are crucial to strong health systems. In most Indian states, local health systems are increasingly being strengthened through decentralisation reforms and understanding how such local initiatives at district and sub-district levels work is crucial to improving responsiveness of health systems to emerging challenges of providing good quality NCD care.

Access to medicines is much more than ensuring availability. In spite of free medicines and care at PHCs on paper, various reasons related to availability of services, acceptability of care, health-seeking behaviour of patients and perceived and technical quality of medicines and healthcare at government PHCs hinder utilisation of medicines, even where medicines are available. In the present study, we hope to better understand how this situation could be changed in favour of improving access to medicines.

### NCD in primary health care

Our intervention somewhat mirrors the much-criticized vertical disease-control approach as it focuses on improving access to medicines for NCD patients *specifically* (and thus not for patients presenting with other problems) and on strengthening processes at the primary level for the care of NCD patients *specifically* (and, again, not for patients presenting with other problems), while not addressing the various underlying reasons for the *general* under-performance of local health systems. A more integrated and less selective approach would have been more appropriate in addressing PHC-wide issues in drugs management and continuity of care rather than take up these issues only in relation to NCDs. The intervention by highlighting NCDs may in fact in some areas decrease focus on other services or activities that are less in the picture and therefore less well-resourced. To some extent, this may be addressed by ensuring that the intervention warrants that health workers privilege their existing services whenever there is a need to choose one against the other. In terms of sustainability of the intervention, since the most of the government health services in India do not currently provide systematic care and follow-up for NCDs, we foresee that the generation of research evidence and positive experiences by the district team during the ATM intervention may result in the incorporation of some of its intervention activities into their annual action plans.

## Abbreviations

ANM: Auxiliary nurse-midwife
ARS: Arogya Raksha Samiti (Health protection committees)
ASHA: Accredited social health activist
ATM: Access to medicines
BCC: Behavioural change communication
FGD: Focus group discussion
LMIC: Low- and middle-income country
LSCS: Lower segment caesarean section
MO: Medical officer
NCD: Non-communicable diseases
NHM: National Health Mission
OOP: Out-of-pocket expenditure
PHC: Primary health centre
WHO: World Health Organization
